## Abstract

**Background:**

Research and policy demonstrate the value of and need for systematically identifying and preparing care partners for their caregiving responsibilities while their family member or friend living with dementia is hospitalized. The Care Partner Hospital Assessment Tool (CHAT) has undergone content and face validation and has been endorsed as appropriate by clinicians to facilitate the timely identification and preparation of care partners of older adult patients during their hospitalization. However, the CHAT has not yet been adapted or prospectively evaluated for use with care partners of hospitalized people living with dementia. Adapting and testing the CHAT via a pilot study will provide the necessary evidence to optimize feasibility and enable future efficacy trials.

**Objective:**

The purpose of this paper is to describe the study protocol for the adaptation and testing of the CHAT for use among care partners of hospitalized people living with dementia to better prepare them for their caregiving responsibilities after hospital discharge.

**Methods:**

Our protocol is based on the National Institutes of Health Stage Model and consists of 2 sequential phases, including formative research and the main trial. In phase 1, we will use a participatory human-centered design process that incorporates people living with dementia and their care partners, health care administrators, and clinicians to adapt the CHAT for dementia care (ie, the Dementia CHAT [D-CHAT]; stage IA). In phase 2, we will partner with a large academic medical system to complete a pilot randomized controlled trial to examine the feasibility and estimate the size of the effect of the D-CHAT on care partners’ preparedness for caregiving (stage IB). We anticipate this study to take approximately 60 months to complete, from study start-up procedures to dissemination. The 2 phases will take place between December 1, 2022, and November 30, 2027.

**Results:**

The study protocol will yield (1) a converged-upon, ready-for-feasibility testing D-CHAT; (2) descriptive and feasibility characteristics of delivering the D-CHAT; and (3) effect size estimates of the D-CHAT on care partner preparedness. We anticipate that the resultant D-CHAT will provide clinicians with guidance on how to identify and better prepare care partners for hospitalized people living with dementia. In turn, care partners will feel equipped to fulfill caregiving roles for their family members or friends living with dementia.

**Conclusions:**

The expected results of this study are to favorably impact hospital-based care processes and outcomes for people living with dementia and their care partners and to elucidate the essential caregiving role that so many care partners of people living with dementia assume.

**Trial Registration:**

ClinicalTrials.gov NCT05592366; https://clinicaltrials.gov/ct2/show/NCT05592366

**International Registered Report Identifier (IRRID):**

PRR1-10.2196/46808

## Introduction

People living with dementia experience frequent and costly hospitalizations, which are associated with poor health outcomes. Compared to other older people, people living with dementia have twice as many hospitalizations and stay nearly a day longer [1]. Moreover, evidence indicates that people living with dementia discharged from hospitals are at higher risk for readmission within 30 days [2,3], urinary tract infections, pressure areas, pneumonia, and delirium [4]. The total costs of these hospital services are more than 3 times greater for people living with dementia than for those without dementia [5]. Further, hospitalizations also hasten the cognitive decline of people living with dementia [6]. Care partners (a traditional family, partner, or other support person designated by the older adult care recipient) have the potential to mitigate these adverse outcomes for people living with dementia when included in care processes during hospitalization.

While more than 11 million care partners of people living with dementia provide nearly 15 billion hours of unpaid care annually [6], many hospitals fail to integrate care partners in the care delivery processes of people living with dementia [7]. Care partners are not included despite our knowledge that frontline approaches to reducing adverse outcomes rely on their unique knowledge of the preferences and functional abilities of people living with dementia [7,8]. In fact, a recent study investigated compliance with the Caregiver Advise, Record, and Enable (CARE) Act, which requires hospitals to (1) provide admitted patients the opportunity to identify and record the name of a care partner; (2) inform the care partner when discharge is to occur; and (3) prepare care partners to fulfill caregiving roles to be performed in the home, like complex medical and nursing tasks [9]. Analyses of more than 200 direct observations and 13,000 patient electronic health records for the first 6 months after implementation of the CARE Act in 1 health care system revealed the following: (1) 53% of patients identified a care partner on admission, 23% declined, and 8% were not asked by a clinician; (2) 97% of care partners identified on hospital admission were not notified of the patient’s upcoming discharge; and (3) only 19% of care partners received preparation on tasks to be performed in the home during the patient’s hospital stay [10,11].

Further, a systematic review of the needs of care partners of people living with dementia across care settings [12] found limited available evidence for identifying and preparing care partners for their caregiving tasks in settings other than the home and community; no studies focused on acute care settings. These findings highlight missed opportunities to individualize care for people living with dementia and to prepare their care partners to fulfill caregiving tasks post hospital discharge. Despite their essential role, care partners who are poorly integrated into hospitalizations and inadequately prepared to fulfill dementia caregiving tasks are at high risk of experiencing excess burden, chronic stress, and depression [13,14].

Clinical decision-support tools offer a valuable resource for addressing this gap in practice as they enable multidisciplinary teams to navigate complex care processes (eg, care partner identification) using structured yet flexible guidance [15]. Common uses of clinical decision-support tools include timely screening for preventable conditions or medical events and ensuring accurate diagnoses [15]. Yet, a recent systematic review uncovered no clinical decision-support tools to guide the systematic identification and preparation of care partners for hospitalized people living with dementia [16].

In response to this gap, we developed and validated a standardized decision-support tool to facilitate the timely identification and preparation of care partners for cognitively unimpaired adult patients during their hospitalization. The Care Partner Hospital Assessment Tool (CHAT) has strong content and face validity and is endorsed as appropriate by clinicians and care partners in the hospital setting [17,18]. Guided by the widely used and effective decision-support model of Screening, Brief Intervention, and Referral to Treatment [19,20], the CHAT applies a sequential screening and referral pathway that (1) identifies care partners and their preferences for involvement in the patients’ hospital care and (2) tailors referrals to address their stated preferences and unmet needs for postdischarge preparedness.

Because there is a great need for a novel decision-support tool in hospital-based dementia care, we will (1) adapt the CHAT for dementia (ie, the Dementia Care Partner Hospital Assessment Tool (D-CHAT)), and then (2) test the feasibility and estimate the size of the effect of the D-CHAT compared to usual care. D-CHAT has the potential to improve hospital-based care processes and outcomes for people living with dementia and their care partners. In addition, findings from this study will further elucidate the essential caregiving role that so many care partners of people living with dementia assume.

## Methods

### Design and Conceptual Framework

The study is based on the National Institutes of Health Stage Model approach [21] to intervention development, focusing on stage 1, and will be conducted in 2 phases: formative research and the main trial. During the formative research phase, we will use a participatory human-centered design process that incorporates people living with dementia and their care partners, health care administrators, and clinicians to refine and adapt the CHAT for hospital-based dementia care (stage IA). During the main trial phase, we will conduct a pilot randomized controlled trial to examine the feasibility and estimate the size of the effect of the D-CHAT on care partners’ preparedness for caregiving tasks (stage IB).

The System Engineering Initiative for Patient Safety 2.0 model (Figure 1) will guide our data collection and analysis to ensure the identification of components influencing the adaptation and delivery of the D-CHAT across all health care system components. This model emphasizes a working system that includes interacting components (ie, people, tasks, tools or technology, organization, and physical environment) that influence health care processes and outcomes [22-24].

**Figure 1 figure1:**
[figure not shown]
System Engineering Initiative for Patient Safety 2.0 model.

### Ethics Approval

The study was approved by the institutional review board on April 11, 2023 (2022-0352). All protocol modifications will be reviewed and approved by the institutional review board as needed.

### Phase 1—Formative Research

#### Sample

Based on established relationships with health system and community partners, we will purposefully select interested parties for two groups: (1) health care administrators and frontline clinicians, and (2) people living with dementia and their care partners that meet eligibility criteria (see Table 1). Each group will form a design team and have 5-7 participants, which is within the standard range used in participatory design research [25]. The small number of participants in groups reduces the potential for groupthink (ie, by having products from one group evaluated by the other) and ensures that all participants have ample time to provide their perspectives [26].

**Table 1 table1:** Sampling plan (N=10-14).

Group			Reason for inclusion		Eligibility criteria
**Group 1 (n=5-7)**					
	Health care administrators	Knowledge and expertise related to the day-to-day operations of hospital, patient eligibility, enrollment, claims, and payment of health services		Have at least 5 years of professional experience in their respective position Speak and understand English	
	Clinicians	Knowledge and expertise related to the delivery of health services		Have at least 5 years of professional experience in their respective position Speak and understand English	
**Group 2 (n=5-7)**					
	People living with dementia	Knowledge and experience related to receiving hospital care		Have experienced a hospitalization Have some form of dementia Identified a care partner	
	Care partners of people living with dementia			Provide unpaid care to a relative or partner living with dementia to help them take care of themselves Be at least 18 years or older Speak and understand English	

#### Data Collection

Teams will complete 5 co-design videoconference sessions occurring in parallel across 4 months, with 2-3 weeks between each session. In session one, we will present the original CHAT. We will lead discussion, interpretation, and respectful debate among design team members to begin to generate the needs of dementia care partners and health care system process changes to optimize their involvement in care. We will ensure progress toward solution convergence from session to session. The design teams will conduct sessions independently, but in between sessions, they will swap solutions and provide feedback, which we will summarize and present in subsequent sessions. Each web-based session will last approximately 90 minutes and will be audio recorded for subsequent analysis. The design process can be conceptualized as a funnel in which we start with divergent ideas and then work toward convergence through the sessions. Participants will receive US $20 after completing each session.

#### Data Analysis

Within the 2-3 weeks between each session, we will review audio recordings as well as any team and participant observation notes, case scenarios, and sketches. Two members of our team will use the Rapid Identification of Themes From Audio Recordings (RITA) method [27] to identify design specifications. The same 2 team members will then combine the themes from the RITA with the synthesized team and participant observation notes, use of case scenarios, and sketches to provide as inputs to participants at the following design session. Following the design session’s completion, we will adapt the CHAT for dementia care, applying input from the final design session, and performing member checking by reviewing changes with members from the groups. This process will produce a converged-upon D-CHAT that is ready for stage 1B feasibility testing [21].

### Phase 2—Main Trial

#### Setting and Sample

This single-blind pilot randomized controlled trial [28] will occur on medical and surgical units at a large academic health care system in the Midwest. This system serves more than 700,000 patients each year with approximately 1849 physicians and 21,000 staff at 7 hospitals. Care partners will be asked to participate if they meet the following inclusion criteria: (1) provide unpaid care to a hospitalized adult relative or partner to help them take care of themselves because of a dementia diagnosis, (2) be at least 18 years or older, and (3) speak and understand English. Care partners of hospitalized adult relatives or partners that are observation or same-day stay patients will be excluded. There will be no exclusion based on sex, gender, race, or ethnicity.

#### Training, Informed Consent, and Screening

Before recruitment begins, we will provide training on the D-CHAT to clinicians in medical and surgical units. To reduce contamination [29], we will instruct trained clinicians to not use the D-CHAT when treating those in the control arm and to not discuss details of the D-CHAT with nontrained clinicians. Once this training is completed, a member of the study team will work with unit coordinators to schedule morning, afternoon, and evening shifts for data screening, consent, and data collection. Institutional review board approval will be obtained to access electronic health records of hospitalized people living with dementia. We will use electronic health records to identify patients who have a documented care partner (or legally authorized representative). Someone who is part of the patient’s care team will then approach the patient’s present care partners to determine their interest in the study. If a care partner expresses interest in participating, a study team will then share study details, obtain written consent, and complete the baseline visit (see Figure 2). A member of the study team will monitor protocol deviations like unintended crossovers by completing weekly, in-person check-ins with the trained clinicians.

**Figure 2 figure2:**
[figure not shown]
Main trial flow diagram. D-CHAT: Dementia Care Partner Hospital Assessment Tool.

#### Baseline Visit

The baseline visit will be completed in a designated room in the hospital to limit distractions. After completing consent, participants will complete descriptive measures and the primary clinical outcome measure (see Table 2). All measures will be administered by a trained, blind assessor. Immediately after these procedures, participants will be randomized to either the intervention or control group, and the clinical team will be notified of the assignment. These efforts will minimize bias and increase internal validity [28].

**Table 2 table2:** Measures.

Study measures		Instrument	Collection method	Time points	
				1^a^	2^b^
**Clinical outcomes**					
	Preparedness for caregiving	The Preparedness for Caregiving Scale	Self-report	✓	✓
	Satisfaction of care	Hospital Consumer Assessment of Health care Providers and Systems	Self-report		✓
	Burden	Zarit Burden Interview	Self-report	✓	✓
	Depression	Patient Health Questionnaire-2	Self-report	✓	✓
**Descriptive measures**					
	Demographic characteristics	Patient and care partner sex, age, race or ethnicity, education, employment status	Self-report	✓	
	Admission status	Patient reason for patient admission	Medical record	✓	
	Dementia characteristics	Patient type and stage of dementia	Medical record	✓	
	Caregiving context characteristics	Care partner relationship to patient, hours providing care, living situation	Self-report	✓	
**Feasibility measures**					
	Recruitment	Number of care partner contacts, screened, consented, and enrolled	Study records		✓
	Attrition	Reasons for absence and attrition	Study records		✓
	Safety	Adverse events from completing the D-CHAT^c^	Study records		✓
	Time to complete measures and D-CHAT	Minutes	Study records	✓	
	Adherence	Reasons for not following the D-CHAT protocol	Self-report		✓
	Implementation satisfaction	Clinician questionnaire	Self-report		✓

^a^Time point 1: preintervention—within 24 hours of the patient’s admission.

^b^Time point 2: follow-up—within 72 hours of the patient’s discharge.

^c^D-CHAT: Dementia Care Partner Hospital Assessment Tool.

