#### Intervention

Care partner participants randomized to the intervention group will receive the D-CHAT and usual care delivered through the patient’s care team. Aftercare partners complete the D-CHAT, and their responses will be given to the unit coordinator to review and make suggested referrals to specified clinicians. These clinicians then use the responses to develop and complete information and skill preparation with the care partners. For example, the D-CHAT could reveal that a care partner does not have the necessary diabetes knowledge or skill set to help give her husband living with Alzheimer disease and diabetes his insulin injections. Information gleaned from the D-CHAT would trigger a diabetes care and education specialist to address the care partners’ caregiving needs.

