#### Usual Care Control

The comparison condition will be the usual care that hospitalized people living with dementia and their care partners receive as part of the large academic health care system. No standardized clinical decision-support tool that facilitates the identification and preparation of care partners is currently used for routine hospital-based dementia care. These care partner participants will complete the same measures as participants in the intervention condition on the same timeline using identical assessment procedures.

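### The Safety row of Table 2 ties adverse events to completing the D-CHAT, so event counts cannot be compared between arms and the later intervention steps are not clearly covered

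*Protocol article*

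**What the plan says.** The only definition of an adverse event in the protocol article is the Safety row under Feasibility measures in Table 2: "Adverse events from completing the D-CHAT". The source is study records. The row is ticked for time point 2 only, which the table footnote places "within 72 hours of the patient’s discharge".

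Exposure to the tool is confined to one arm. Under Intervention, "Care partner participants randomized to the intervention group will receive the D-CHAT and usual care". Under Training, Informed Consent, and Screening, "we will instruct trained clinicians to not use the D-CHAT when treating those in the control arm".

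The Intervention section describes a sequence. Care partners "complete the D-CHAT, and their responses will be given to the unit coordinator to review and make suggested referrals to specified clinicians". After that, "These clinicians then use the responses to develop and complete information and skill preparation with the care partners".

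For controls, the Usual Care Control section says: "These care partner participants will complete the same measures as participants in the intervention condition on the same timeline using identical assessment procedures".

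Under Clinical outcomes, Table 2 also lists the Zarit Burden Interview and the Patient Health Questionnaire-2 at both time points.

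**The concern.** A safety measure is most useful when the event is defined without reference to the treatment and its cause is judged afterwards. Here the cause is part of the definition. That has three consequences.

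- A person who never received the D-CHAT cannot have a qualifying event, so there is no background rate against which to read the intervention-arm count.
- If completing the D-CHAT means answering it, an event that arises during referral or skill preparation falls outside the wording, although those steps are where care partners are actually prepared.
- Whether an event enters the count depends on someone deciding that the D-CHAT caused it. An event not so attributed leaves no trace in this measure.

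At stake is how far the pilot's adverse-event count can inform the later efficacy trial. The preparedness estimate is not at stake.

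**Working it through.** The plan states no figure for safety, so there is none to reproduce. The main check is a comparison of passages; the arithmetic only shows what a two-arm count could offer.

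**Step 1: can a control participant have a qualifying event?** Table 2 requires that the event come from completing the D-CHAT. The Intervention section gives the D-CHAT to the intervention group, and the training section tells clinicians not to use it for controls. The control count is therefore zero by construction, except where an unintended crossover occurs.

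**Step 2: what does completing cover?** In the Intervention section, care partners complete the D-CHAT first; coordinator review, referral and skill preparation come after. Table 2 uses the word in the same way in its timing row, where time to complete the measures and the D-CHAT is recorded in minutes at time point 1. Both uses point to the answering step. Against this, the Sample Size Justification and Data Analysis sections speak of the effect of the D-CHAT and mean the whole intervention. The narrow scope is the nearest reading, but the article does not state an exclusion.

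**Step 3: does the row fit the control-arm text?** The Usual Care Control section promises the same measures and identical procedures in both arms. An event defined by its origin in the D-CHAT cannot be assessed identically in people who did not receive it. The article does not say how the two are to be reconciled.

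**Step 4: what harm-related data exist in both arms?** Burden and depression are collected at both time points, and the Usual Care Control section applies the same measures to controls. Changes in these scores can be compared.

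**Step 5: precision.** Inputs: 64 per arm, or 56 per arm with follow-up data (Sample Size Justification). The article gives no event rate, so rates p of 5%, 15% and 25%, equal in both arms, are assumed.

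One arm only, no events seen: the one-sided 95% upper bound is 1 − 0.05^(1/n).
- n = 64: 1 − 0.05^(1/64) = 4.6%
- n = 56: 1 − 0.05^(1/56) = 5.2%

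This bounds the rate of attributed events in the intervention arm and gives no contrast with control.

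Both arms: the 95% CI half-width of the risk difference is 1.96 × √(2p(1 − p)/n).

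| Assumed p | n = 64 per arm | n = 56 per arm |
|---|---|---|
| 5% | 1.96 × √(0.095/64) = 0.076 | 1.96 × √(0.095/56) = 0.081 |
| 15% | 1.96 × √(0.255/64) = 0.124 | 1.96 × √(0.255/56) = 0.132 |
| 25% | 1.96 × √(0.375/64) = 0.150 | 1.96 × √(0.375/56) = 0.160 |

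At 5% the half-width exceeds the rate itself, so a two-arm count would be descriptive only.

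**The case against.** The strongest reply is that this is a short table cell in a condensed article. Elicitation, relatedness grading and reporting by arm usually belong in the full protocol, which is not shown. The trial aims at feasibility and effect-size estimation and has no comparative safety objective. Neighbouring feasibility rows, such as adherence to the D-CHAT protocol, are also specific to the intervention. The promise of identical measures may concern instruments that participants fill in, whereas Safety comes from study records. And a risk difference at this sample size would say little.

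Much of this stands. It keeps the point small and weakens the conflict with the Usual Care Control section. It does not remove the point, because the article does more than leave a detail out: it states a definition, and that definition restricts the count to one arm and to attributed events.

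Some stronger readings are tempting, and the article does not support them:

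- *Harm cannot be compared at all.* Burden and depression scores are available in both arms at both time points; only adverse-event counts lack a comparison.
- *Nothing is recorded for controls.* The article does not say so. The wording cannot count a control event, and the text on identical procedures is left unreconciled with it.
- *Referral and skill preparation are excluded.* This is the nearest reading, not a stated rule.
- *Causes are judged by staff who know the allocation.* The article does not say who judges. Attributing an event to the D-CHAT presupposes knowing that the person received it, but no assessor is named.
- *Background events would pile up in the D-CHAT arm against none in control.* Under a rule that counts only attributed events, unrelated events should be counted in neither arm.

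**Conclusion.** The point holds as a minor defect in a stated definition. As worded, the Safety row cannot count an event in the control arm apart from crossover, most naturally covers only the answering step, and builds attribution into the count. The adverse-event counts therefore allow no between-arm comparison.

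The size is modest. The primary estimate, the sample size and the stated objectives are unchanged. Recording events in both arms would give a descriptive control rate, with a risk difference known to within about 8, 12 or 15 percentage points at 64 per arm and slightly less precisely at 56. Those figures rest on assumed event rates of 5%, 15% and 25%, equal in the two arms, and on a normal approximation that is rough at the lowest rate. The reading of the wording rests on the article alone; a fuller protocol might already define adverse events independently of the D-CHAT.

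**What to change.** Reword the Safety row of Table 2 along these lines: adverse events in care partners from randomization to time point 2, in both arms, elicited with the same scripted question at the follow-up phone assessment. Record relatedness as a separate item, naming the D-CHAT itself, the referral and the skill preparation as distinct possible sources. Keep the question free of any mention of the D-CHAT so that it can be put identically to both groups. Report counts by arm descriptively; if a risk difference is given, show its confidence interval and make no claim of comparative safety.

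The cost is one question on a call that both arms already receive, some additional event forms, and the logging of background events unrelated to the intervention. The change should be made before data collection, because control-arm events that were never asked about may not be recoverable later.
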